### Outcomes

**Table 1** provides an overview of our primary, secondary and other outcomes, including the specific tool used to measure the outcome and measurement time point.

**Table 1 T1:** Overview of data collection.

Domain	Data Collection Tool	Time Point	Variable Type
Post-Traumatic Stress Disorder Symptom Severity	PTSD CheckList – Civilian Version (PCL-C) (44)	Baseline and every 60 days	Primary Outcome
Substance Use	Addiction Severity Index (45)	Baseline and every 60 days	Primary Outcome
Demographics	Age, race, ethnicity, gender (assigned at birth and current identity), relationship status, level of education, income level, employment status, health insurance status and provider, housing status	Baseline evaluation	Covariates
Criminal Activity Involvement	Criminal Justice Questionnaire (developed by first and second author)	Baseline and every 60 days	Secondary Outcome and Predictor
Motivation to Change	The Change Questionnaire (46)	Baseline and every 60 days	Secondary Outcome and Predictor
Treatment Satisfaction	Client Satisfaction Questionnaire (CSQ-8) (47)	Baseline and every 60 days	Secondary Outcome and Predictor
Quality of Life	36-Item Short Form Survey Instrument (SF-36) (48)	Baseline and every 60 days	Secondary Outcome and Covariate
Past Barriers to Substance Use Treatment	Barriers Questionnaire (49)	Baseline and every 60 days	Secondary Outcome and Covariate
Perception of Recovery	The Questionnaire about the Process of Recovery (QPR) (50)	Baseline and every 60 days	Secondary Outcome and Covariate
Self-Stigma	Substance Abuse Self-Stigma Scale (51)	Baseline and every 60 days	Secondary Outcome and Covariate
Substance Craving	3-Item Substance Craving Scale (52)	Baseline and every 60 days	Secondary Outcome and Covariate
Emergency Department Utilization	Services Use Questionnaire and EHR (developed by first and second author)	Baseline and every 60 days	Secondary Outcome and Covariate
Hospital and/or treatment facility utilization	Services Use Questionnaire and EHR (developed by first and second author)	Baseline and every 60 days	Secondary Outcome and Covariate

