#### Effectiveness of the multi-level intervention

Two primary outcomes will inform our assessment of effectiveness: change in PTSD symptom severity [as measured by the Post-Traumatic Symptom Checklist (44)] and change in substance use [as measured by the Addiction Severity Index (45)]. We will use a pre-post intervention multilevel regression model analysis to examine the change in our primary outcomes of interest. The goal of the multilevel models will be to look for significant and meaningful change in the pre-post scores of our primary outcomes, PTSD symptom severity and substance use, based on the impact of the client’s predictor variables; criminal justice involvement, motivation to change and client treatment satisfaction (see **Table 1**).

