To assess the impact of our covariates and secondary outcomes of interest, we will apply a multi-step approach to examine the significance of our independent variables. First, we will test for significant pre-post differences in our secondary outcomes to assess the impact of the variables from the start to finish of the client’s time in the program using parametric paired t-tests. Results of the paired tests will provide results to the significance of the impact pre-post on the client’s perceptions of the program and will provide validation of using the markers as covariates in the regression model. Second, we will apply two change-score multilevel regression models; one for the PTSD symptom severity outcome and one for the substance use outcome, with control variables (age, race, ethnicity, gender, relationship status, level of education, income level, employment status, health insurance status, provider and housing status), significant secondary outcome variables (quality of life, past barriers to substance use treatment, perception of recovery, self-stigma, substance craving, emergency department utilization and hospital treatment facility utilization) and predictor variables mentioned above. Examination of the multilevel regression model will allow for examination of client level deviation of the outcome variables by the time and predictor variables. *Post-hoc* analysis of the correlation matrix and pairwise t-tests of secondary outcomes and pre-post measurement will be examined to understand the impact of the markers in relation to the full scale of the data. Models will be used to assess for statistical robustness using the variance inflation factor for multicollinearity and appropriate error distribution tables. Latent-trait variables will be assessed for internal validity using exploratory factor analysis and reliability using Cronbach’s Alpha measure of internal consistency. While the primary outcome endpoint will be 120 days post-baseline, we will conduct secondary analyses to examine outcomes for participants using the last follow-up date post-baseline.

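### Both primary models admit secondary outcomes as covariates because they changed during treatment; if entered as changing values, the model no longer estimates total pre-post change

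*Protocol article*

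**What the plan says.** All of this is in the protocol article.

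- **Target.** Under Effectiveness of the multi-level intervention: "Two primary outcomes will inform our assessment of effectiveness: change in PTSD symptom severity", with change in substance use as the second. The multilevel models are to "look for significant and meaningful change in the pre-post scores of our primary outcomes, PTSD symptom severity and substance use". The design is non-randomized and the planned analysis is pre-post with no comparison group, so the mean change is the effectiveness estimate.
- **Screen.** The same section continues: "First, we will test for significant pre-post differences in our secondary outcomes", by paired t-test. A significant result "will provide validation of using the markers as covariates in the regression model".
- **Models.** "Second, we will apply two change-score multilevel regression models; one for the PTSD symptom severity outcome and one for the substance use outcome". Besides demographic controls and three predictors, these contain the "significant secondary outcome variables (quality of life, past barriers to substance use treatment, perception of recovery, self-stigma, substance craving, emergency department utilization" and hospital or treatment-facility use: up to seven variables.
- **Measurement.** Table 1 under Outcomes gives each of the seven the role "Secondary Outcome and Covariate", measured at baseline and every 60 days. The three predictors (criminal justice involvement, motivation, satisfaction) are also listed as secondary outcomes on that schedule.

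No other model is given for the primary outcomes. The text does not say whether the admitted variables enter as baseline values, follow-up values or changes.

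**The concern.** A paired t-test on a secondary outcome shows that the variable moved between two visits. It does not show that the variable confounds the pre-post comparison or predicts the primary outcome. What the rule does select is variables that changed during treatment. Craving, self-stigma, perceived recovery and quality of life are plausible routes by which the programme would act on PTSD symptoms and substance use, or parallel results of it.

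Holding the movement of such variables fixed answers a different question: how much the primary outcome changed apart from what accompanied the changes in the covariates. The gap between that quantity and the total change depends on which secondary outcomes pass the screen, by how much they moved and in which direction. Both primary analyses are affected, and the reported effect could differ materially from what participants experienced.

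**Working it through.** **The plan's own figure.** Under Sample size, 101 is derived for a paired t-test with a moderate effect (no number given), alpha 0.05 and power 0.80. A conventional moderate standardised change of 0.5 needs 34 people two-sided or 27 one-sided. N = 101 corresponds to about 0.28 two-sided or 0.25 one-sided. So 101 is not reproduced from 0.5, and cannot be settled without the numeric effect. This point does not depend on it; 101 is used below only as the number analysed.

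**Set-up.** Let the change in the primary outcome have mean d, and let each of k admitted covariates change by mean m. All are in SD units of change, signed so that positive is improvement, with common correlation r among all the changes. Regress outcome change on the raw covariate changes. Each slope is r / [1 + (k − 1)r], so the intercept, which is the adjusted pre-post change, is

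d − m × kr / [1 + (k − 1)r].

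The document gives none of d, m and r, so all three are assumptions. For m, an observed change passes the screen at n = 101 once it exceeds 1.984 / √101 = 0.197 SD. Hence 0.2 SD is about the smallest that gets in; 0.5 SD is taken as a large case.

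**Multiplier kr / [1 + (k − 1)r].**
- k = 3: 0.9/1.6 = 0.5625 at r = 0.3; 1.5/2.0 = 0.75 at r = 0.5
- k = 7: 2.1/2.8 = 0.75 at r = 0.3; 3.5/4.0 = 0.875 at r = 0.5

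**Adjusted change when the true change is 0.50 SD.**

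| Covariates | Change in each | r = 0.3 | r = 0.5 |
|---|---|---|---|
| 3 | 0.2 SD | 0.50 − 0.2 × 0.5625 = 0.388 | 0.50 − 0.2 × 0.75 = 0.350 |
| 3 | 0.5 SD | 0.50 − 0.5 × 0.5625 = 0.219 | 0.50 − 0.5 × 0.75 = 0.125 |
| 7 | 0.2 SD | 0.50 − 0.2 × 0.75 = 0.350 | 0.50 − 0.2 × 0.875 = 0.325 |
| 7 | 0.5 SD | 0.50 − 0.5 × 0.75 = 0.125 | 0.50 − 0.5 × 0.875 = 0.063 |

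Simulation at n = 101 agrees with the formula. Two-sided power is above 0.99 unadjusted. It stays at about 0.95 or higher in the 0.2 SD rows. In the 0.5 SD rows it falls to about 0.49 and 0.26 with three covariates, and 0.19 and 0.10 with seven. If the true change is only 0.28 SD (unadjusted power 0.80), three covariates that each change by 0.2 SD bring power to about 0.40 and 0.34.

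**Other directions.**
- One covariate worsens by 0.5 SD, r = 0.3: 0.50 + 0.5 × 0.3 = 0.65, an inflated effect.
- No change in the outcome, three covariates each improve by 0.5 SD, r = 0.3: 0 − 0.5 × 0.5625 = −0.28, an apparent worsening that is significant in about 70% of simulated trials.

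**Multilevel form.** The change-score result carries over to a two-occasion random-intercept model with time-varying covariates. With the standardised change near 0.28 and equal covariate changes, the time coefficient (outcome units) went from −0.249 to −0.179 with one covariate (28% lost) and from −0.251 to −0.051 with seven weakly related ones (80% lost).

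**Forms of entry that do no harm.** With baseline-only covariates, or change covariates centred at their means, the estimate stayed at 0.50 with power above 0.99.

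**The case against.** The strongest objection is that the form of entry is not stated. A condensed article may leave it to the full plan, and two possible forms (baseline values, mean-centred changes) leave the estimate intact. That stands, and it makes the bias conditional. It does not rescue the rule: a screen on change has little purpose for covariates entered at baseline, the section goes on to examine deviation by time, and under any form the screen is unrelated to prognosis.

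A reader might infer that adjustment simply removes the treatment effect, or always biases towards no effect. The documents do not support either. Only the part shared with the covariates is taken out. The direction depends on how the covariates move, and nothing shows that past barriers, emergency visits and facility use will all improve alongside the outcome. The near-total losses need every covariate to pass the screen with a large change.

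The models are also partly explanatory: the section wants change related to the three predictors and speaks of assessing the impact of covariates. That is fair, and it means the primary estimand is unclear as well as exposed to bias. But the section also names pre-post change as the goal and offers no other model for it.

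**Conclusion.** The point holds in conditional form. The stated admission rule is wrong in itself: significant change in a secondary outcome is no ground for adjusting a primary pre-post analysis for it. If the admitted variables enter as change, follow-up or time-varying values, the time effect or intercept is not the total pre-post change the section seeks.

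For a true change of 0.5 SD and changes that are all in the beneficial direction, the loss with three to seven covariates runs from about 22% (0.50 to 0.388) to about 88% (0.50 to 0.063). That range rests on assumed effect sizes and correlations, so confidence is high on the rule and only moderate on the size. With other patterns of movement the estimate can be too large or have the wrong sign. Because the rule governs both primary analyses, it should be corrected before the data are analysed.

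**What to change.** 1. State as the primary estimate, for each primary outcome, the time effect at 120 days (the endpoint the article already names) from the multilevel model, either unadjusted or adjusted only for a short prespecified list of baseline covariates.
2. Delete the rule that a significant paired t-test admits a variable as a covariate.
3. Analyse the secondary outcomes as outcomes. Label any model that includes their changes, or post-baseline values of the three predictors, as an exploratory association or mediation analysis, and state the form in which each variable enters.

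This changes analysis wording only and needs no new data. The cost is that the richer explanatory model, including the question of how criminal justice involvement, motivation and satisfaction relate to change, becomes secondary or exploratory.

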**Methods:**

We are using a Type 1 hybrid implementation design with a non-randomized approach (ISRCTN registration # ISRCTN33100750). We aim to enroll 110 adults (
≧18
) who screen positive for unhealthy use of alcohol, prescription medications (used nonmedically) and/or illicit drugs. Peer support workers are responsible for screening, using MI to increase engagement in screening and treatment and delivery of SS. Pharmacotherapy is provided by addiction clinical specialists. Treatment is provided post hospital discharge via telehealth to increase access to care. Participants are identified through (1) review of electronic health records for individuals with a chief or secondary complaint or mental health condition relating to alcohol and/or other drug use, (2) referrals from clinical staff and (3) screening in the ED and medical inpatient units. Feasibility is being measured through process data. Effectiveness will be determined by changes in two primary outcomes: (i) PTSD symptom severity; and (ii) substance use.

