### Sample size

We estimated our sample size using GPower (version 3.1.9.7) and focused on a meaningful change from baseline to six-months on the primary outcome PTSD symptom severity via a t-test means difference between two dependent means. The expected mean change in PTSD symptom severity as measured by the PCL-C was based on findings from research conducted by the first author in which PSWs implemented SS to a similar population (36). Assuming a moderate effect size, with an alpha = 0.05, and power = 0.80 the GPower analysis determined that a total sample size of 101 would be needed.

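### Each primary change model takes 14 to 21 named variables for at most 101-110 clients, a sample sized for a paired t-test with no covariates, and enters insurance status and insurer as separate terms

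*Protocol article*

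**What the plan says.** The Effectiveness section of the protocol article plans two change-score multilevel regressions, one for PTSD symptom severity and one for substance use. Each is fitted "with control variables (age, race, ethnicity, gender, relationship status, level of education, income level, employment status, health insurance status, provider and housing status"). To these 11 it adds "significant secondary outcome variables (quality of life, past barriers to substance use treatment, perception of recovery, self-stigma, substance craving, emergency department utilization" and hospital or treatment-facility use), seven candidates in all, each admitted only if its own pre-post paired t-test is significant. Three predictors complete the model: criminal justice involvement, motivation to change and treatment satisfaction. The same section sets the primary endpoint at 120 days and plans a variance inflation factor check, with no statement of what follows from it.

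The Sample size section rests on a different analysis, "via a t-test means difference between two dependent means". It reports that "the GPower analysis determined that a total sample size of 101 would be needed", and the abstract states "We aim to enroll 110 adults". The Discussion reports that enrolment has run below expectation. Table 1 lists the insurance items together as "health insurance status and provider", so the term 'provider' in the regression list is read here as the insurer.

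**The concern.** The section states its aim as change in the primary outcomes in relation to the three predictors, so individual coefficients carry the conclusion. Those coefficients are to come from models with 14 to 21 variables, mostly categorical among the controls, in about a hundred clients at best. The power statement was made for the mean of a single paired difference and says nothing about a coefficient in such a model. At stake are the precision and stability of the predictor estimates and the credibility of any reported model fit.

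The controls also do little for the other target, the mean change. Each client serves as their own comparison, so stable demographics are not needed to estimate it. Two of the controls, insurance status and insurer, carry overlapping information and cannot both enter as free terms.

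**Working it through.** **The plan's own figure.** The stated inputs are "Assuming a moderate effect size, with an alpha = 0.05, and power = 0.80". No numerical effect size and no sidedness are given. From the noncentral t distribution, a paired t-test at the conventional moderate d=0.5 needs 34 clients (two-sided) or 27 (one-sided). A requirement of 101 appears at d=0.25 one-sided, or at d of about 0.28 two-sided. So 101 is not reproduced from a conventional moderate effect. That is a separate matter. What counts here is that the calculation contains no covariates.

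**Counting variables.** 11 controls + 3 predictors = 14 if no secondary outcome qualifies; 14 + 7 = 21 if all do.

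**From variables to parameters (assumption).** The article gives no category levels. Coarse, middle and fine codings, counting the intercept, give 17, 29 and 40 parameters with no secondary outcome, and 24, 36 and 47 with all seven. The range is therefore roughly 17 to 47.

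**Formulas**, with p slopes and n clients:
- clients per slope = n/p
- R-squared expected with no true effect = p/(n−1)
- residual df = n−1−p
- standard error of a predictor relative to a 3-slope model, independent regressors = √[(n−5)/(n−p−2)]
- power for one predictor, two-sided 5%: noncentral t with n−p−1 df and noncentrality b√(n−p). Setting 80% power at n=101, p=1 gives b=0.283.

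Results at n=101:

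| p | clients per slope | chance R-squared | residual df | SE ratio | power |
|---|---|---|---|---|---|
| 14 | 7.2 | 14/100 = 14% | 86 | 1.06 | 74% |
| 21 | 4.8 | 21/100 = 21% | 79 | √(96/78) = 1.11 | 0.283√80 = 2.53, giving about 70% |
| 37 | 2.7 | 37% | 63 | √(96/62) = 1.24 | 0.283√64 = 2.26, giving about 61% |
| 47 | 2.1 | 47% | 53 | 1.36 | 0.283√54 = 2.08, giving about 53% |

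Counting the intercept or not shifts p by one and power by about one point or less. With 110 clients and p=21 there are 110/21 = 5.2 clients per slope and a chance R-squared of 21/109 = 19%.

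**Bias check.** In 3,000 simulated data sets per setting with no true effect and a fixed covariate set (n=101), type I error for one coefficient was 4.7% with 3 slopes, 4.8% with 21 and 4.6% with 36, and the mean coefficient stayed within 0.004 of zero. Its standard deviation rose from 0.102 to 0.114 and 0.124, and mean R-squared from 3% to 21% and 36%. The loss is in precision and apparent fit.

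**Insurance pair.** Take provider with levels none, A, B and C (an illustration).
- If the uninsured are coded 'none', then insured = A + B + C exactly. Intercept, status and three provider columns make 5 columns of rank 4, so one term is aliased.
- If provider is blank for the uninsured and only complete cases are used, they leave the model and status becomes constant.

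**The case against.** Several points on the other side stand. The parameter count beyond 21 is a coding assumption, and 21 is itself a ceiling because the secondary outcomes enter conditionally. The loss at 21 parameters, from 80% to about 70%, is moderate. Demographics may confound the associations between the predictors and change, so adjusting for some of them has a purpose. With 'none' coded, software drops the aliased column, no client is lost and fitted values are unchanged; the planned variance inflation factor check should expose the dependence, although no action is attached to it.

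Three stronger readings are tempting and are not supported:
- **That the coefficients are biased or their tests invalid.** For a fixed covariate set the simulation shows neither. That reassurance does not extend to secondary outcomes admitted by significance, because the simulation did not cover selection.
- **That complete cases will collapse.** Independent missingness of 1%, 2% or 3% per variable would leave 101 × 0.99^21 = 82, 101 × 0.98^21 = 66 or 101 × 0.97^21 = 53 clients. But the article states neither a missingness rate nor a missing-data method, and an article may leave the method to the full plan.
- **That uninsured clients will be excluded.** This needs a blank provider field and complete-case fitting, and neither is stated.

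It could also be said that a multilevel model with several follow-ups has more rows than clients. The primary endpoint is a single 120-day change, and extra rows do not add clients to support client-level covariates.

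**Conclusion.** The concern holds as a mismatch between the primary models and the sample. The count of 14 to 21 named variables comes directly from the text, as does the sizing of 101 on a test without covariates. At 21 parameters and n=101 the consequences are 4.8 clients per parameter, 21% chance R-squared and about 70% power for a predictor that would have 80% alone. The power figures assume independent regressors, no gain in residual variance from the covariates, and all 101 clients analysed; since enrolment is behind, 101-110 is an upper range. The 61% and 53% figures also rest on assumed codings.

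The damage is imprecision, instability and optimistic fit in the predictor part of the analysis. The within-client mean change does not need these controls. The insurance pair is redundant on the Table 1 reading; whether it costs a term or costs clients depends on coding and missing-data choices that the article does not give.

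**What to change.** - Make the unadjusted within-client change at 120 days the primary estimate of mean change for each primary outcome. This is the form of analysis that the sample size was based on. The Sample size section works from six months, and that difference in time point should be reconciled separately.
- For the predictor associations, name a short set of baseline covariates in advance, with collapsed categories, and do not admit secondary outcomes by significance.
- Replace insurance status and provider with one variable that has 'uninsured' as a level.
- Report the full-list model as exploratory, and state what will be done if the variance inflation factor check shows collinearity.

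This changes analysis wording only and needs no new data. The cost is fewer adjusted associations in the main analysis. It should be settled before the primary models are fitted, since trimming covariates after seeing results would itself be data-driven.
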